**FIGURE 1 pri1969-fig-0001:**
[figure not shown]
Flow diagram

### Sample size

2.5

To determine a medium effect size of the intervention on adherence to the activity advice after 12 weeks in the intervention group compared to the control group, Power G sample size calculation is performed. With an alpha of 0.05% and a power (1‐beta) of 80%, 142 patients are needed. With an expected overall drop‐out rate of 15%, a total of 163 patients is needed.

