### Statistical methods

2.9

To analyse the data SPSS version 25.0 (IBM SPSS, Chicago, IL, USA) will be used. For demographic data descriptive statistics will be used and normality assumptions for the variables will be checked. An intention‐to‐treat analysis will be used for the main outcome. To correspond to the primary aim of the study, outcomes of the Activ8 will be dichotomized into adherent and not adherent patients in the intervention and control group. The Chi^2^ test will be used to investigate if there is a significant difference in the proportion of adherent patients to the activity advice between the intervention and control group after one, six and 12 weeks, and if there is a significant difference in the proportion of adherent patients between patients who experienced social support or not on the social support scale after 12 weeks. A Time Series Analysis will be used to present changes over time in perceived illness beliefs of patients and partner/friend. To understand whether illness beliefs influence adherence, Pearson's r between outcomes of the IPQ‐S at baseline and after 12 weeks and (non)adherence measured by the Active8, will be calculated, and linear regression will be used for modelling the relationship between these outcomes. To assess the correlation between attitude and intention to physical activity (MAI) and adherence at 12 weeks, Pearson's will be calculated, and linear regression will be used for modelling the relationship between these outcomes. Influence of age, gender, education level, comorbidity (CIRS), pain (VAS) and disability (QBPDS) on adherence, will be estimated by multiple regression analyses. A *p* value of <0.05 will be considered statistically significant.

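### Sample size (2.5): the total of 163 does not leave 142 patients after 15% drop-out, and alpha is printed as 0.05% where the analysis uses 0.05

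*Protocol article*

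**What the plan says.** The Sample size section (2.5) of the protocol article gives the whole calculation in three sentences:

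- Aim: "To determine a medium effect size of the intervention on adherence to the activity advice after 12 weeks".
- Error rates and number to be analysed: "With an alpha of 0.05% and a power" … "of 80%, 142 patients are needed".
- Allowance for loss: with 15% drop-out expected, "a total of 163 patients is needed".

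The section does not give the effect-size index or its value, the adherence proportions expected in each arm, whether the test is one- or two-sided, or which test the calculation was made for.

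Statistical methods (2.9) dichotomises adherence, compares the two arms with a chi-square test and sets the threshold: a p "value of <0.05 will be considered statistically significant".

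**The concern.** The recruitment total should follow from the number to be analysed and the expected drop-out, and it does not. The alpha in the sample-size section should be the level at which the trial is analysed. As printed, it is 100 times smaller.

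At stake are the recruitment target and the reader's ability to reconstruct the design. If drop-out runs at the rate the plan expects, the trial ends with fewer evaluable patients than the plan says it needs. A reader who takes 0.05% literally is told of a far stricter error rate than the one in use. Because the medium effect is not specified, the reader also cannot recover the intended design from 142.

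**Working it through.** **Inputs from the documents.** Evaluable number 142, power 80%, drop-out 15%, total 163 and alpha 0.05% (all section 2.5). Significance level 0.05 and a chi-square test on adherent versus not adherent in two arms, a 2×2 table with 1 degree of freedom (section 2.9).

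**Assumptions, because the documents are silent.** Two-sided testing and equal allocation.

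**1. Drop-out allowance**

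- The printed total is reproduced by multiplying by one plus the drop-out rate: 142 × 1.15 = 163.3, printed as 163.
- If a fraction d of those enrolled is lost, N(1 − d) remain. Keeping 142 therefore needs N = 142/(1 − 0.15) = 167.06, so 168. Check: 167 × 0.85 = 141.95, just short; 168 × 0.85 = 142.8.
- With 163 enrolled, 163 × 0.85 = 138.55 remain, about 138.
- The loss that 163 can absorb is (163 − 142)/163 = 12.9%.

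Effect on power: for a 1-df chi-square at two-sided 0.05, 80% power needs a noncentrality of (1.960 + 0.842)² = 7.849. For the effect that 142 patients detect with that power, 138 patients give 7.849 × 138/142 = 7.628. Power is Φ(√7.628 − 1.960) = Φ(0.802) = 78.9%. No effect-size index is needed, because noncentrality scales with the number of patients.

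**2. Alpha**

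Read literally, 0.05% is 0.0005. Under that reading, with a conventional medium effect and 80% power:

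- w = 0.3, 1 df: noncentrality (3.481 + 0.842)² ≈ 18.68; N = 18.68/0.3² = 207.6, so 208.
- h = 0.5 for two proportions: 300 in total.
- d = 0.5 for a t-test: 306 in total.

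At 0.0005, 142 patients would give 53.8% power for w = 0.3. None of these readings brings 142 within reach, so the calculation was very probably made at 0.05.

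**3. What 142 corresponds to at alpha 0.05**

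| Reading of a medium effect (two-sided 0.05, 80% power) | Total N |
|---|---|
| w = 0.3, uncorrected 2×2 chi-square: 7.849/0.09 = 87.2 | 88 |
| h = 0.5, arcsine | 126 |
| d = 0.5, t-test | 128 |
| h = 0.5, two proportions with continuity correction, control rate 10% to 60% | 142 to 152 |
| w = 0.3, chi-square with 5 df | 143 |

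The continuity-corrected reading gives exactly 142 for some rates. For 40% versus 64.7%, the uncorrected size is n = 62.99 per arm, and the corrected size is (n/4)·[1 + √(1 + 4/(n × 0.247))]² = 70.86, so 71 per arm. A control rate of 30% with h = 0.5 also gives 142. The 5-df reading does not fit a 2×2 table.

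If w = 0.3 with 1 df was meant, 142 is more than needed: power would be 94.7%.

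**The case against.** The best defence is that nothing of substance turns on either figure. The allowance is 5 recruits short, which costs about one point of power, and 15% is itself only an expectation. If the medium effect was w = 0.3 on an uncorrected test, power at 138 patients is still 94%. The alpha is an obvious slip, since section 2.9 gives 0.05. A journal article also condenses a longer protocol, which may state the effect size.

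Most of this stands, and it sets the severity. It does not remove the errors: the article prints both figures, one fails on the plan's own inputs and the other contradicts the plan's own threshold.

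A reader might infer three stronger things that the documents do not support:

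- **That 142 is the wrong size for a medium effect.** It does not match w = 0.3 on an uncorrected 2×2 chi-square, which needs 88. But section 2.5 names no index, rates or test, section 2.9 does not say whether the chi-square is corrected, and h = 0.5 with continuity correction can give exactly 142. The figure is unverifiable, not refuted.
- **That the trial is badly underpowered because alpha is 0.0005.** The analysis threshold and the size of 142 both point to a misprint.
- **That a null result could not be interpreted.** It would be read from the observed difference in adherence and its confidence interval, whatever index was used in planning.

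**Conclusion.** Wrong as written, and minor. The total of 163 fails on the section's own inputs. The number consistent with 142 evaluable patients and 15% drop-out is 168, and this rests on no unstated assumption. At 163, about 138 patients remain and power is about 79% for the effect that 142 detects at 80%, assuming a 1-df test at two-sided 0.05.

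The alpha of 0.05% contradicts section 2.9. That it is a misprint is an inference, but a strong one.

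The basis of 142 should be stated so that it can be checked. On this evidence it should not be called an error.

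**What to change.** In section 2.5:

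1. Print alpha as 0.05 and state whether the test is one- or two-sided.
2. Either give the total as 168, or keep 163 and state that about 138 patients are expected to be evaluable at 15% loss, with about 79% power for the effect that 142 detects at 80%.
3. Replace the bare reference to a medium effect with the index, its value and the test actually used, including any continuity correction, and the adherence proportions if they entered the calculation. These must come from the sponsor's own calculation. An effect size solved backwards from 142 should not be put in its place.

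The cost is a text correction. If 163 is kept, the stated power falls by about one point; if 168 is chosen, five more patients are enrolled.

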### Recruitment

2.6

Recruitment is scheduled from October 2016 till December 2022. To achieve adequate patient enrolment, next to own consultation of patients experiencing non‐specific low back pain by participating physiotherapists, referring health care providers, such as general practitioners located in the city of the participating practices will be informed about the study, to send patients with non‐specific low back pain to those physiotherapists.

### Assignment of interventions

2.7

It is hypothesised that patients in the intervention group adhere better to the activity advice than patients in the control group. It is also hypothesized that patients having a BMI >25 and patients experiencing >3 episodes of NSLBP are potentially more inactive and non‐receptive to the interventions on adherence. To prevent influence of these factors on study outcomes, stratification is applied on these variables. Therefore, a concealed randomization sequence is prepared by the randomisation centre of the Maastricht University. Randomization will be performed with a block size of four, with strata for BMI (<25, >24) and number of previous episodes of low back pain (2–3, >3).

Investigators, patients, partners or friends and participating physiotherapists are blinded to the allocation and outcomes. To prevent that patient and their partners/friends of both groups will meet in the waiting room appointments of patients treated in the intervention or control group in the same private practice must be planned on different days or sections of the day. Physiotherapist are blinded for participating in the intervention group or control group. To ensure blinding of the physiotherapists, where their training is separate, it will be emphasized not to communicate about the interventions to each other during the investigation period.

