## METHODS

2

This study is a double blinded multicentre randomized controlled trial, with a concealed randomisation. This protocol was conducted according to Standard Protocol Items: Recommendations for Interventional Trials (SPIRIT) guidelines.

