During the first meeting all physiotherapists will be informed about the Dutch guideline for low back pain (Staal et al., 2013) and state of the art knowledge, to provide that treatment during the study will be in accordance with the guideline. Before the second meeting participating physiotherapists will be divided into three groups: in every clinic, an Assessor Physiotherapist (AP), an Intervention Group Physiotherapist (IGP) and a Control Group Physiotherapist (CGP) is needed. The second meeting will be for AP's, IGP's and CGP's separately. The AP's will be trained in knowledge about the study, inclusion criteria, exclusion criteria, informed consent, standardized intake forms and assessments. They will be trained how to communicate about the study in a positive manner to the patient and partner/friend. It will be explained to the physiotherapists how to adhere to the allocation procedure and how to register all investigational procedures and the use of the activity monitor. Participating CGP's will be instructed on the background and rationale of the study, treatment of illness beliefs, the activity advice, and the use of the activity monitor. Participating IGP's will be instructed on the same elements with an additional short course on how to motivate the patient and their partner/friend in organizing social support. Some participating physiotherapists are students Orthopaedic Manipulative Physical Therapy at the Rotterdam University of Applied Sciences, Rotterdam, The Netherlands. They participate in this study as APs where they must conduct a management assignment as part of their Master of Science educational program.

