### Timeline

2.4

Eligible patients will be recruited for the study together with their partner or friend by the assessing physiotherapist and will receive information about the study. If patients and partners or friends decide after 1 week of consideration they want to be included in the study, written informed consent will be asked to the patient and partner or friend and base‐line assessment of the patient and partner or friend will be performed (Appendix 1). After base‐line assessment the assessor explains to the patient that further treatment will be performed by an IGP or CGP. The patient will be contacted within 2 days for an appointment with either the IGP or CGP. The patient and partner/friend will be instructed to come both to the next two appointments. The assessor contacts the randomization centre. The randomisation centre allocates the patient for IGP or CGP and informs the assessor. The assessor instructs the IGP or CGP to make the next appointments with the patient and their partner/friend.

After the first intervention on illness beliefs with or without organizing social support, treatment will be applied according to the Dutch guideline for low back pain (Staal et al., 2013). In both groups' patients are instructed in executing the activity advice in accordance with the DSHPA and to wear a move monitor for 1 week (Hildebrandt et al., 2007). In the group in which the social support is given, the partner/friend will be asked to make a week schedule of times, activities, and contact‐control moments for the coming months.

At the end of the week the activity monitors will be returned, and questionnaires will be filled out. The second intervention on illness beliefs with or without organizing social support takes place and treatment will be applied according to the Dutch guideline for low back pain (Staal et al., 2013). After six‐ and 12‐weeks patients will be invited by the assessors to wear the Active8 for one week and to fill in the questionnaires. During the study period the IGP contacts the partner/friend in week 6 and 10 to evaluate whether social support was given. At the last appointment also the partner or friend will be invited and asked to fill in questionnaires. Enrolment of the study is shown in the flow diagram (Figure 1).

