### Data management

2.8

Patient data will be coded and the key to the codes will be safeguarded by the secretary of the randomization centre of the Maastricht University. These codes are unknown and not accessible for the researchers. Outcomes of questionnaires and Activ8 will be collected by the assessing physiotherapist. Losses‐to‐follow‐up and respective reasons will be recorded. The researchers collect the data from the assessors every month and enter the data in an electronic database. Access to the data obtained in this research will be restricted to the researchers involved in the collection and analysis of the data. The handling of personal data complies with the General Data Protection Regulation (GDPR) (EU, 2018). Study files will be kept for 15 years.

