## DISCUSSION

3

This project is the first comprehensive research project to assess whether social support influences adherence to an activity advice outside the clinical setting without supervision of a healthcare provider. Unique in this study is that intervening on illness beliefs will be provided to patient and partner to minimize the influence of maladaptive illness beliefs on adherence. Literature mentions that intervention on illness beliefs changes outcomes of the DIPQS, however, responsiveness of the questionnaire is lacking (Broadbent et al., 2015). Despite this, it is of interest if a tendence of change over time may occur and influence outcomes of adherence.

Where evidence on clinical barriers is conflicting and limited, complementary, influence of age, gender, education level, comorbidity, attitude and intention to physical activity and perceived pain and disability on adherence will be investigated. Findings have implications for the management of patients with low back pain, enabling prediction as to which low back pain patient giving an activity advice with social support makes sense.

It is important to note the variation in how concepts of (non)adherence are operationalized in existing literature resulting in variable outcomes (Essery et al., 2017; van Koppen et al., 2020). For robust outcomes in this study an accurate definition of the activity advice is applied, mentioning frequency and duration, and outcomes of adherence are dichotomous, measured with a validated move monitor.

Strengths of the study are the concealed allocation and the randomization. To reduce the presence of observer bias, measurements will not be performed by the treating physiotherapist.

Treatment of both groups in one physiotherapy practice is preferred to overcome selection bias. This implicates that despite the standardized protocol and the strict requirements to ensure blinding, it is possible that patients and treating physiotherapist exchange information about the interventions. This may influence outcomes and is therefore a limitation of the study.

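### The trial is described as double blinded with physiotherapists blinded, yet the assessor who runs follow-up and collects the outcomes is told each patient's allocation

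*Protocol article*

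**What the plan says.** The Methods section opens with the label: "This study is a double blinded multicentre randomized controlled trial". Assignment of interventions spells out who is meant: besides investigators and patients, "partners or friends and participating physiotherapists are blinded to the allocation and outcomes". It makes no exception for assessors, and it adds: "Physiotherapist are blinded for participating in the intervention group or control group".

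The Participants section sets up three physiotherapist roles in every clinic: an assessor (AP), an intervention-group therapist (IGP) and a control-group therapist (CGP). IGPs receive an extra course on organising social support.

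Timeline describes the allocation step. The assessor contacts the randomisation centre, and then: "The randomisation centre allocates the patient for IGP or CGP and informs the assessor". The assessor next has the named therapist make the appointments. At weeks 6 and 12 it is again the assessors who invite patients to wear the monitor and fill in the questionnaires. Data management states: "Outcomes of questionnaires and Activ8 will be collected by the assessing physiotherapist".

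Against observer bias, the Discussion offers that "measurements will not be performed by the treating physiotherapist".

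**The concern.** The article claims a design property that its own procedure removes. The person told the arm is the person who arranges the later monitor weeks and gathers the data. The 12-week comparison, on which the sample size is based, depends on that follow-up.

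Two things are at stake. The first is an avoidable opening for bias: an assessor who knows the arm may, without intending it, differ in how firmly they explain monitor wear, pursue a late monitor or go through the self-reported scales. The second is accuracy of reporting. A results paper that repeats the present wording would claim blinding of physiotherapists that did not exist, and readers would judge risk of bias on that claim.

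**Working it through.** No figure is in dispute, so the check is to set the statements side by side, role by role.

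1. **Assessor and allocation.** Assignment of interventions covers participating physiotherapists without exception. Participants makes the assessor one of them. Timeline has the centre inform the assessor whether the patient goes to the IGP or the CGP. These statements cannot all be true.

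2. **Does the therapist's label reveal the arm?** The abbreviations stand for intervention group and control group, and the allocation message is expressed in those terms. Each clinic is described as needing one of each, so the therapist's identity also points to the arm.

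3. **Assessor and outcomes.** Data management gives the assessor collection of both Activ8 and questionnaire outcomes, with no exception. Timeline gives the assessor the invitations at weeks 6 and 12. Knowledge of the arm and handling of the outcomes therefore sit in one role. Week 1 is less clear: the instruction to wear the monitor follows the first treatment session, and Timeline does not say who gives it.

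4. **The stated safeguard.** Separating the assessor from the treating therapist means that nobody measures the results of their own treatment. It does not stop the assessor knowing the arm, because the arm has been sent to them.

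5. **Treating therapists.** IGPs take the social-support course, hold the standardised discussion with the partner or friend, and contact that person in weeks 6 and 10 to see whether support was given. They cannot be blind to what they deliver. At most they could be unaware of how the other group differs, which is a different and weaker property.

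6. **Where influence could enter.** The primary outcome is walking and cycling recorded by the device, with adherence set at 5 or more times a week of at least 30 minutes. The assessor does not rate it. It still requires the patient to wear the monitor for a week and return it, so instructions and follow-up can affect what is recorded and what is missing. The Social Support Scale, the DIPQ-S and the MAI are self-reported by patient and partner and gathered by the assessor.

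7. **Reach.** Every allocation takes this route, so all 163 planned patients are affected. The article gives nothing from which an effect on the adherence proportions could be calculated.

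**The case against.** The best defence is that masking here means something narrower. APs, IGPs and CGPs are trained in separate meetings and told not to discuss the interventions, and patients of the two groups are seen at different times. On that reading the assessor knows which colleague treats the patient but not what the arm contains. The article does not say so, however. It uses labels that name the group, and it trains assessors in knowledge about the study. Its words are that physiotherapists are blinded to the allocation, and the allocation is exactly what the assessor receives.

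The second defence is that an accelerometer records the primary outcome and that patients and partners fill in the questionnaires themselves. This stands as a limit on the likely bias. It does not restore the blinding that is claimed.

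Two stronger readings are tempting and should not be adopted:

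- **Control therapists and the hypothesis.** A reader might infer that control therapists are taught the social-support hypothesis, because they "will be instructed on the background and rationale of the study", and that contamination follows. The article does not say what that background contains, and it lists the social-support course as an addition for IGPs only. It also provides separate training and a no-communication instruction, and it admits possible exchange of information within a practice as a limitation. The text supports no change to the control therapists' training on this ground.
- **Direction of bias.** A reader might infer that any bias favours the intervention, through more prompting to wear and return the monitor. Nothing in the article establishes a direction.

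**Conclusion.** The contradiction is explicit. The trial is described as double blinded with physiotherapists blinded to allocation, while the stated procedure tells the assessor each allocation and gives that assessor the later follow-up invitations and the outcome collection. The claim is also untenable for IGPs with respect to what they deliver. The conclusion rests only on reading Timeline and Data management as written, and on the IGP and CGP labels meaning what Participants says they mean.

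It is a real and avoidable weakness that should be corrected. It does not invalidate the primary comparison. The device-recorded primary outcome limits the exposure, and the size and direction of any bias are unknown. The article's claim about investigators is not contradicted by these sections. For patients, it does not say what they are told about the hypothesis, so this review neither confirms nor disputes their blinding.

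**What to change.** 1. **Allocation route, for patients still to be randomised.** The randomisation centre sends the allocation directly to the IGP or CGP, or to the practice desk, who books the patient. The assessor is told only that the patient has been randomised.

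2. **Social Support Scale.** Because its answers may reveal the arm, have patient and partner complete it last, after all other assessments, or return it sealed.

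3. **Blinding statement.** Replace the double-blind label and the sentence on physiotherapists with a role-by-role account. Treating therapists are not blinded to what they deliver. Assessors knew the allocation for patients randomised under the current route. For later patients, describe the steps taken to keep the assessor unaware; do not assert that they succeeded, since assessor and therapists work in the same practice.

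**Cost.** A changed message route, a small change in how one questionnaire is handled, and the loss of the double-blind label. No extra staff. Recruitment was scheduled from October 2016 to December 2022, so the new route cannot undo disclosure for patients already randomised. If few or none remain to be randomised, the corrected statement is still feasible and is the essential part.
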